**HIV testing**

All household members will be offered HIV testing after counselling, in the first instance using a serial rapid diagnostic test algorithm, the kits for which will be provided provided by the Provincial Departments of Health. Research Assistants trained and accredited in HIV testing and counselling. In line with recommendations in the World Health Organization’s HIV Testing Services Guidelines 2015, a negative A1 test result will diagnose participants as HIV-negative. Positive results to both Tests A1 and the confirmatory A2 test will diagnose participants as HIV-positive. Where results to Test A1 and A2 are discrepant, both tests will be repeated, and followed by a tie-breaker using a laboratory-based 4^th^ Generation ELISA (anticipated in <1 per 1000 participants). Couples testing will be provided if requested.

Children under 18 months of age will have a dried blood spot sample taken for HIV PCR testing as per South African National Guidelines, with testing performed at the National Institute for Communicable Diseases. Results-based post-test counselling will be offered individually in a private setting out-of-earshot and out of sight of other household members.

Participants declining HIV testing may be offered alternative laboratory-based HIV testing on either a blood specimen or an oral fluid specimen using OraQuick, OraSure Technologies –depending on their availability, with communication of results within one week, but if still reluctant to be HIV tested, will be asked to provide an anonymous oral fluid sample for HIV testing for study purposes. Those who request anonymous testing without receipt of results and those who refuse HIV testing will be encouraged to go to a HIV testing facility for testing.

All participants who test HIV positive will be referred to their nearest clinic for initiation of ART. We will draw blood specimen for CD4 count estimates -if still required by National Guidelines as these are expected to change to a test and treat approach in the near future – as soon as the participant is diagnosed with HIV. Participants who test HIV positive will receive supported access to HIV treatment, prearranged by the study at their nearest HIV care clinic.

**Other measures**

Weight and height will be measured in all participants, for children under one year, we will measure their length while recumbent.

Blood pressure will be measured in all adults over 18 years, using standardised method, at least three times with the patient seated using an electronic calibrated device with an interval of at least three minutes between each reading, each reading will be recorded with the time that it was measured. This measure will be repeated at the follow up household visit if the blood pressure is elevated. Any person requiring antihypertensive treatment according to current South African guidelines will be referred to initiation of therapy.

Random finger prick glucose level will be measured in all participants over 30 years of age. Those with measures >10 mmol/l will have an HbA1C taken and referred for treatment if elevated.

**Follow-up household visit (1week after baseline household visit)**
Xpert MTB results and results of laboratory HIV testing (and CD4 counts and HbA1C as appropriate) will be communicated to participants by study staff including registered nurses at a follow-up household visit approximately one-week after the baseline assessment is completed. Participants with microbiologically-confirmed tuberculosis or diagnosed with HIV will be supported to attend their nearest local primary care clinic to register for ongoing care and treatment.

Participants who are older than 5 years of age or test HIV-negative and whose sputum tests are negative for TB and whose tuberculin skin test is negative will be dispensed the first month of IPT by study nurse and then referred for ongoing preventive treatment at their local clinics with a clear referral letter that includes all results. Additionally all those participants who are less than 5 years of age or are HIV-positive and sputum tests are negative for TB will be dispensed the first month of isoniazid preventive therapy by study nurses, Linkage to care will be confirmed by collection of referral cards at study facilities by study staff. Home tracing to encourage re-entry to care will be undertaken on three occasions for participants who do not attend clinics within 2 weeks of referral.

Should any liquid TB culture be resulted positive after this visit, a visit will be made to the few anticipated households from where this result was taken to inform the patient and refer him/her for TB treatment.

| **Age of household member** | **HIV status** | **TST Required** | **Active TB disease** | **TB HH contact** | **IPT initiated** | **Study procedure** |
| --- | --- | --- | --- | --- | --- | --- |
| Child < 5 years | POSITIVE on ART or not | NO | NO | YES | YES | Initiate 1 month IPT |
| Child ≥5 years, adult or adolescent | POSITIVE on ART or not | NO | NO | YES | YES | Initiate 1 month IPT |
| Child < 5 years | NEG | NO | NO | YES | YES | Initiate 1 month IPT |
| Child ≥5 years, adult or adolescent | NEG | YES | NO | YES | YES | Initiate 1 month IPT |

Table 1. IPT initiation for household contacts without TB symptoms

*Final intervention household visit (3 months after baseline household visit)*
All intervention households will be visited once at approximately three months after the initial assessment. This visit will be offered because our previous data suggests that a significant proportion of household members with either TB, or HIV, diagnosed at the baseline household visit, do not access care or treatment. Patients not accessing TB treatment, ART or IPT care will be reassessed and assisted to start appropriate treatment, with study staff attempting to overcome access barriers identified by this group. In addition, we will reassess whether those with hypertension or those diagnosed with type 2 diabetes mellitus were started on appropriate therapy and are at this visit controlled or have a plan for future care. Household members requiring other assistance or care will receive supported access to their local health facility or to the Department of Social Development to access social grants. Moreover, at this visit a TB symptom screen on all available household members not on TB treatment will be done, with investigation of those with symptoms, using Xpert and TB culture. We will not visit the household again to interview household members not present at this single final intervention visit.

All visits will be recorded including the number and level of staff members and the purpose and duration of the visit.

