2. HIV testing with prompt initiation of both antiretrovirals and TB preventive treatment for HIV-infected contacts according to current South African guidelines,
3. Preventive therapy for tuberculin skin test-positive, HIV-negative **and** HIV-infected household contacts without active TB disease;
4. A three-month supportive follow-up visit to confirm treatment receipt, and assist those who have either not accessed care and treatment; or who have experienced problems with their treatment; or who have developed symptoms of TB in the interim.

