In the intervening period since the final ZAMSTAR prevalence survey in 2010, there have been considerable advances in TB diagnosis, and prevention. Routine TB diagnostics have improved markedly with the widespread scale-up of the Xpert MTB/Rif molecular TB diagnostic platform (Boehme CC, 2010) (and more recently with a newer, apparently more sensitive version the Xpert Ultra not yet available for use). Xpert MTB/Rif reduces diagnostic delay and results in earlier TB treatment initiation (Theron G, 2014); TB preventive treatment guidelines for HIV-infected individuals have evolved to recommend long-term, more effective regimens (Samandari 2011, Martinson 2011), that when co-administered with antiretroviral therapy (ART), are safe and reduce mortality and TB disease (TEMPRANO ANRS 12136 Study Group 2015, Rangaka 2014). The CD4 threshold for initiating ART has been raised to 500 cells/mm3 and likely will be redundant when the test-and-treat strategy is implemented; and first line ART regimens have been simplified to single daily dosing with fixed-dose combination tablets. Moreover, children diagnosed with TB are increasingly being recognized as important sentinel cases for rapid identification of an infectious household TB case (Puryear,2013; Lala, 2014). Finally our data shows that HIV-seronegative household contacts in a high burden setting in the year after a household contact tracing intervention have annual TB incidence of 700/100,000 (van Schalkwyk, 2014) – suggesting preventive treatment against TB should be offered to HIV seronegative adults and older children in contact with a case, although this is not currently part of guidelines for preventive treatment in South Africa.

**We therefore hypothesise that a household intervention that actively includes these recent improvements will improve TB free survival** **and decrease the prevalence of new TB infections in children**.

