**Secondary objectives:**

1. To assess the effectiveness of isoniazid preventive treatment on new cases of TB in HIV-seronegative individuals who are tuberculin skin test positive.
2. To compare the yield and costs of IHCS versus standard of care in identifying undiagnosed cases of TB and undiagnosed or untreated HIV
3. To compare rates of linkage to TB treatment between participants identified with TB through IHCS and standard of care
4. To explore perceptions and acceptability of doing home visits with household members

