**Sputum Collection**

To avoid bias related to collecting better quality sputum samples from symptomatic patients, we will collect one spot sputum sample from all household members capable of producing a sputum sample, before we ask about TB symptoms. Prior to producing a sputum specimen household members will be asked to drink a cup of water and rinse out their mouths, then take four deep breaths prior to giving a good cough effort. If small volumes of sputum are obtained, we will allow up to three hours for the collection of a spot sputum specimen. This specimen will be subjected to Xpert MTB/Rif (or the at time-of-study current version of the usual first line TB lab test in the public sector) and liquid mycobacterial culture at public sector laboratories. Single sputum specimens will be at least 3ml and at the lab will be mixed with decontaminant as per standard operating procedures in the two public sector laboratories we will send specimens to - then split into two: Xpert MTB Rif (with subsequent addition of buffer) and immediate liquid culture in the MGIT automated system as per current protocols in public sector mycobacterial laboratories. We will record the cycle threshold number of the Xpert and the time-to-positive in liquid culture. Sputum samples will be immediately stored and transported in coolboxes at 4ºC to public sector laboratories for testing. Anyone who tests positive for *M tuberculosis* will be immediately referred to their chosen public sector clinic for TB treatment initiation with a clear referral letter. For those who are Xpert MTB/Rif negative, HIV-negative and over 5 years of age a tuberculin skin test will be performed with the needle of the syringe parallel to the long axis of the arm at this initial visit and read 48 – 72 hours later using the ball-point pen to mark the widest transverse diameter measured with the reverse calliper method in millimetres. No induration will be documented as 0mm.

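### The 1-week dispensing sentence gives isoniazid to skin-test-negative HIV-negative contacts, the reverse of the intervention as defined, and Table 1 does not settle which is meant

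*Protocol*

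**What the plan says.** The Executive Summary lists the components of the intervention. Component 3 is "Preventive therapy for tuberculin skin test-positive, HIV-negative" contacts without active TB, and it names HIV-infected contacts in the same phrase. The Secondary objectives agree on the HIV-negative group: item 1 concerns isoniazid "in HIV-seronegative individuals who are tuberculin skin test positive".

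Under Sputum Collection, the baseline visit selects people for testing: "For those who are Xpert MTB/Rif negative, HIV-negative and over 5 years of age a tuberculin skin test will be performed".

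The section on the follow-up household visit at one week tells study nurses whom to dispense to. It opens: "Participants who are older than 5 years of age or test HIV-negative and whose sputum tests are negative for TB". It then adds the skin-test condition: those "whose tuberculin skin test is negative will be dispensed the first month of IPT by study nurse". The next sentence covers the remaining contacts and sets no skin-test condition: "Additionally all those participants who are less than 5 years of age or are HIV-positive and sputum tests are negative for TB".

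Table 1, in the same section, has four rows defined by age and HIV status. The fourth, for HIV-negative contacts aged 5 or over, ends "adult or adolescent | NEG | YES | NO | YES | YES | Initiate 1 month IPT". Its columns record whether a skin test is required and whether isoniazid preventive therapy (IPT) is initiated. No column gives the skin-test result.

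**The concern.** The sentence that puts the drug in participants' hands names the opposite skin-test result from the one that defines the intervention. A nurse who follows it would give isoniazid to HIV-negative contacts outside the defined target group, and would give no study-dispensed isoniazid to the contacts the component was written for.

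Staff cannot look elsewhere for the rule. The Background states that preventive treatment of HIV-negative adults and older children is not part of current South African guidelines, so the protocol is the only source.

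At stake are participant care and the content of the randomised intervention. Secondary objective 1 is also exposed: under the literal sentence, the group it names would receive no study-dispensed isoniazid. The exploratory cohort comparison of intervention-arm contacts who do and do not receive IPT also depends on who was eligible to receive it.

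**Working it through.** There is no stated figure to reproduce, and no formula applies. The check sets every statement of the rule side by side.

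**Step 1: which skin-test result triggers treatment.** Take an HIV-negative contact older than 5, sputum negative, with a skin test that has been read.

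| Source | Skin test positive | Skin test negative |
|---|---|---|
| Executive Summary, component 3 | IPT | no IPT |
| Dispensing sentence, 1-week visit | no IPT | IPT |
| Table 1, fourth row | result not named | result not named |

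The Executive Summary and the dispensing sentence disagree in 2 of 2 result categories.

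**Step 2: can the table decide?** Its fourth row has two readings. If a required test means a qualifying test, the row fits whichever result is meant to qualify. Read literally, it starts IPT in everyone tested, which matches neither of the other two statements. On neither reading does it show which result is intended.

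**Step 3: can anything else decide?** Secondary objective 1 points to a positive result. The baseline testing step fits a rule that depends on the result, because testing would serve no purpose in selecting people for IPT if everyone tested were treated. No statement in the protocol, apart from the sentence itself, supports a negative result as the trigger. The weight of the text therefore favours 'positive', but nothing expressly overrides the dispensing sentence.

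**Step 4: who else the sentence covers.** Because age and HIV status are joined by 'or', the sentence also takes in two further groups:
- HIV-positive contacts older than 5. The second row of Table 1 requires no skin test for them, and the next sentence already covers them.
- HIV-negative children under 5. The third row requires no skin test for them, and the next sentence already covers them.

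Both groups therefore fall under two sentences, one with a skin-test condition and one without.

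**Step 5: the age limit.** Take an HIV-negative child aged exactly 5 and read each limit strictly.
- Sputum Collection (over 5): not tested.
- Dispensing sentence (older than 5): covered only through the 'or' clause on HIV status.
- Next sentence (less than 5): not covered.
- Table 1 (5 or over): fourth row, test required.

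Changing only 'or' to 'and' would drop this child from both sentences, so the age limit has to be corrected at the same time.

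**Step 6: the Executive Summary itself.** Read in full, component 3 attaches skin-test positivity to HIV-infected contacts too. Table 1 and the second dispensing sentence require no skin test for them. This is a separate, smaller mismatch, and correcting the dispensing sentence alone would leave it in place.

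**The case against.** The strongest reply is that this is a one-word slip. The Executive Summary, secondary objective 1 and the baseline testing step all point to a positive result, so a careful reader can recover what was meant. That is probably right about the intention. It does not remove the need for correction, because the faulty sentence is the instruction that nurses follow and the table beside it does not put it right.

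A reader might go further and say that the protocol holds three incompatible rules, or that both statements at the 1-week visit give isoniazid to skin-test-negative contacts. The text does not support that. Table 1 omits the qualifying result and does not state a rule of its own. It treats everyone tested only on a literal reading, and that reading would leave the baseline skin test with no part in the decision.

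A reader might also cite the Background for a treat-all rule, since its argument carries no skin-test condition: "suggesting preventive treatment against TB should be offered to HIV seronegative adults and older children in contact with a case". That is a rationale drawn from incidence and sets no procedure. Nor does the three-month visit state a second eligibility rule. It helps people who are not accessing care to start appropriate treatment.

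The analytic reach is limited, and that part of the objection stands. Secondary objective 1 has no matching entry in the list of secondary outcomes. The nearest analysis, exploratory outcome 1, is stratified by HIV serostatus and not by skin-test result. The age-limit differences matter only for a child aged 5.

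**Conclusion.** The point holds as a contradiction between the defined intervention and its dispensing instruction. For HIV-negative, sputum-negative contacts aged 5 or over, the two give opposite answers for both skin-test results. Table 1 leaves the matter open in one of its four rows. The 'or' in the same sentence is a second fault: it overlaps the next sentence and conflicts with the table's exemptions. It need not withhold treatment, since the next sentence covers those groups without a skin test.

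This conclusion assumes that the sputum and skin-test conditions in the dispensing sentence apply to everyone the sentence names, which is its natural reading.

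The number of contacts affected cannot be derived, because the protocol gives neither skin-test positivity nor the age-by-HIV distribution of contacts. The primary outcome definition and the sample size do not depend on this rule. A reader might infer that the wrong contacts were actually treated. The protocol does not show which rule was applied in the field, so that inference is unsupported.

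The correction should be made regardless, because the sentence governs who is given a drug and what the intervention arm receives.

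**What to change.** Subject to confirmation by the clinical leads:

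1. Reword the dispensing sentence so that it covers participants who are 5 years or older **and** HIV-negative, with sputum negative for TB and a **positive** skin test.
2. State in the fourth row of Table 1 that IPT is initiated only if the skin test is positive. Adding the millimetre threshold there would help.
3. Change the age limit for skin testing under Sputum Collection to 5 years or older, so that a child aged exactly 5 is handled the same way throughout.
4. Clarify in component 3 of the Executive Summary that HIV-infected contacts receive IPT without a skin test, as in the second dispensing sentence and Table 1.

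If visits have already taken place, establish which rule staff used, so that secondary objective 1 can be interpreted.

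The cost is a protocol amendment and a notice to staff. There is no statistical cost.

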**Inclusion Criteria for Index Cases**

1. Any patient (living or recently deceased) diagnosed with TB at any health facility in the study districts in the six weeks prior to recruitment.
   1. For index cases with TB older than 7 years of age, laboratory confirmation of **pulmonary TB disease** is required, evidenced by hard copy lab report of at least one of: a smear positive result for acid fast bacilli (graded as +, ++, or +++); an Xpert MTB/Rif test or other WHO recommended molecular assay positive for *M. tuberculosis*; a mycobacterial culture positively identified as *M tuberculosis*; or a histology/cytology report from a biopsy that includes lung tissue that is suggestive of TB disease. LF-LAM may be used to assist in the diagnosis of TB in HIV positive patients with signs and symptoms of TB (pulmonary and/or extrapulmonary) who have a CD4 cell count less than or equal to 100 cells/μL, or HIV positive patients who are seriously ill regardless of CD4 count or with unknown CD4 count. Evidence of a hard copy of recorded LF-LAM result is required.
2. For index cases 7 years and younger, the diagnosis of **TB of any organ** will be evidenced by – at a minimum- firstly: a recorded diagnosis of TB and its anatomical site in any clinic or hospital record; and secondly the prescription of multidrug TB treatment by a doctor for a child with signs and symptoms suggestive of TB. The presence of signs or symptoms suggestive of TB may be obtained either from the clinical record or from the caregiver.
3. Permanent resident in a household with at least one other person in either the Capricorn Health District or the Matlosana Municipality for a total of at least three months in the six months prior to recruitment.
4. Either the participant, the parent or next of kin of a participant declare they have no plans for relocation of their household to another municipality or health district during the course of follow up.

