## Index case identification and consent procedures

A team of enrolled nurses will recruit index cases. They will be equipped and trained to use N95 or other appropriate respiratory protection and infection control measures and also in Good Clinical Practice. They will visit hospitals, clinics and TB laboratories in the catchment areas of the study on repetitive, frequent cycles, to identify potential index cases diagnosed in the past six weeks. Index cases and the parents of index cases younger than 18 will be approached to obtain consent for their own participation in the case of index cases; and in the case of parents of an index case, consent for participation of their child in research Using sensitive approaches, we will attempt to obtain consent from the close next-of-kin of patients with TB who died in hospital/ or at home. Deceased patients who were diagnosed with TB will only be enrolled into the study if date of death is no more than 6 weeks from date of enrolment. If a potential index case of any age is too unwell to comprehend the informed consent process, the research team will approach close next-of-kin of the patient with TB and ascertain if they would give consent for the participation of the index case and his/her household in the study. For this study close next-of-kin are: current spouse living together for past year in the same household, sibling older than 25 years of age, biological parent or biological grandparent – the latter if parents are not available or have passed away.

Adults sputum positive for acid fast bacilli, or with a cycle threshold (Ct) on Xpert MTB/Rif of ≤24, and those with drug resistant TB will take precedence for recruitment, in the event the study capacity to recruit eligible households is exceeded.

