## Procedures for all index case TB participants

After obtaining informed consent, enrolled nurses will administer a baseline index case demographic and clinical questionnaire (including presence and duration of symptoms, comorbid conditions, treatment received and laboratory confirmation of TB). Additionally, the study staff will obtain from each index case a handwritten household census comprising the first two letters of the first name and first two letters of the last name and ages and genders of all of their household members.

Index TB cases will continue to receive TB treatment and HIV testing and care through routine clinical services according to South African National Guidelines. Results of routine TB and HIV investigations completed by the health facility (sputum smear, sputum TB culture, Xpert MTB/Rif, HIV-test, CD4 count, HIV viral load), TB category (pulmonary, extra-pulmonary); and treatment initiation dates will be extracted from clinical records and recorded by study staff using data extraction forms).

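### Study nurses start isoniazid in household contacts without checking the index case's documented drug resistance, although drug-resistant index cases are eligible and can be recruited first

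*Protocol*

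**What the plan says.** **Who can be an index case.** The inclusion criteria open with "Any patient (living or recently deceased) diagnosed with TB at any health facility in the study districts in the six weeks prior to recruitment", followed by diagnostic requirements that depend on age. Drug resistance is not among the exclusion criteria. The section on index case identification adds that "those with drug resistant TB will take precedence for recruitment, in the event the study capacity to recruit eligible households is exceeded".

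**Who gets isoniazid.** The section on the one-week follow-up household visit describes two groups. Contacts in the skin-tested group are "dispensed the first month of IPT by study nurse and then referred for ongoing preventive treatment at their local clinics". Contacts under 5 years or HIV-positive, with negative sputum, "will be dispensed the first month of isoniazid preventive therapy by study nurses". For the skin-tested group, the clinic referral is made "with a clear referral letter that includes all results". Table 1 has columns for age, HIV status, skin test, active disease, contact status and isoniazid. All four rows end in starting one month of isoniazid.

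**Which guideline is cited.** Item 2 of the intervention in the Executive Summary covers "TB preventive treatment for HIV-infected contacts according to current South African guidelines". Item 3, on skin-test-positive contacts, carries no such reference. The Background says of preventive treatment for HIV-negative adults and older children: "although this is not currently part of guidelines for preventive treatment in South Africa".

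**What is recorded on the index case.** The extraction list names "sputum smear, sputum TB culture, Xpert MTB/Rif, HIV-test, CD4 count, HIV viral load", then TB category and treatment dates. No isoniazid susceptibility result is listed.

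**The concern.** The protocol foresees drug-resistant index cases and, to apply its precedence rule, must know of the resistance at recruitment in at least some of them. The dispensing rule then makes no use of that knowledge. A contact infected by an isoniazid-resistant household strain would take isoniazid with less expected benefit, and neither the study nurse nor the receiving clinic is prompted to consider this. The first month is the study's own act and comes before the clinic takes over. This is a treatment rule fixed in the protocol's text and in a table, not an analytic detail that an analysis plan would settle.

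**Working it through.** No figure in the protocol bears on this point, so the check is mainly a comparison of sections.

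1. **Can a resistant index case enter?** Yes. The inclusion criteria do not bar it, the exclusions are silent on it, and the recruitment section gives it precedence under a capacity condition.

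2. **Does the dispensing rule ask about the index strain?** No. The conditions in the one-week visit text are the contact's age, HIV status, sputum and, for one group, skin test. No column of Table 1 concerns the index case's results.

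3. **Does another section supply the check?**
   - Index case procedures: Xpert MTB/Rif and culture are extracted but not linked to the isoniazid decision.
   - Executive Summary item 2: national guidelines govern preventive treatment of HIV-infected contacts (first two rows of Table 1), so an exception may exist there.
   - HIV-negative children under 5 (third row): the protocol does not say whether a guideline governs the nurse's first month.
   - HIV-negative contacts aged 5 or over (fourth row): item 3 cites no guideline, and the Background places this treatment outside current national guidance.
   - Referral letter: it carries all results, but nothing says these include the index case's resistance, and it takes effect after the first month is dispensed.
   - Three-month visit: it follows up contacts not in care and screens for symptoms, well after the first dose.

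4. **Could the information be available in time?** Often. Diagnosis may precede recruitment by up to six weeks, the household is first visited within 14 days of recruitment, and isoniazid is dispensed about a week after that. Index cases diagnosed by smear, histology or LF-LAM, or clinically in young children, may have no resistance result. The point is therefore confined to documented resistance.

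5. **Scale, by assumption only.** Inputs are 2,400 index cases and a mean household size of 5.5 (Sample size). The allocation ratio is not stated; 1:1 is assumed.
   - Intervention households: 2,400 / 2 = 1,200.
   - Per 1% of index cases with documented resistance: 1,200 × 0.01 = 12 households.
   - Contacts, if 5.5 includes the index case: 12 × (5.5 − 1) = 12 × 4.5 = 54.
   - Contacts, if it does not: 12 × 5.5 = 66.
   - The protocol gives no resistance share. An assumed 2% to 10% would be 24 to 120 households, and between 24 × 4.5 = 108 and 120 × 5.5 = 660 contacts.

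These are listed contacts in all four rows, before sputum and skin-test screening. They are not counts of people who would receive isoniazid.

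The one-week visit text asks for a negative skin test where the Executive Summary asks for a positive one. That is a separate inconsistency, and neither version checks the strain.

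**The case against.** **Table 1 is a summary.** It does not state which skin-test result qualifies and lists no clinical contraindications, so a missing column need not be an instruction. An operating procedure might add the check. That is possible, but the accompanying text is equally unconditional, and such a procedure would have to override a stated yes in every row.

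**Other safeguards exist.** The letter, the three-month visit and the adverse-event item on misread HIV or TB results leading to treatment in error all offer something. None makes the nurse consult the index case's results before the first month.

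**Exposure is uncertain.** This stands. Precedence applies only when capacity is exceeded, the drug is not named, and many index cases may have no result. How often contacts carry the household strain is also unknown; estimating the share of transmission due to household exposure is an exploratory aim that depends on further funding.

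**Stronger readings to avoid.**
- A reader might infer from the Background that no outside rule can cover HIV-negative contacts aged 5 or over. It says only that preventive treatment for them is not in the guidelines. National guidance might still address contacts of resistant cases whatever their HIV status, and it is not at hand.
- The drug-resistant TB beds described at the Matlosana hospital might be taken to show how common resistance is among index cases. They are bed capacity at a hospital that takes outside referrals.
- A count of contacts treated inappropriately would need an age, HIV and skin-test breakdown that the protocol does not give.
- Nothing in the protocol shows direct injury or a distorted primary comparison. The stated consequence is reduced expected benefit.

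**The comparator letter is also silent on resistance.** True, but there clinics decide under national guidelines and the study dispenses nothing.

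**Conclusion.** The point holds in limited form. As written, the protocol has study nurses start isoniazid in contacts of index cases whose drug resistance is documented, a group it expects to enrol. The gap is plainest for HIV-negative contacts aged 5 or over, because the protocol cites no guideline that would supply an exception; for HIV-infected contacts the cited guidelines may do so. That benefit is reduced rests on the premise that isoniazid does less against a strain resistant to it, and applies only to contacts who carry that strain. The number affected cannot be derived; the figure per 1% of index cases shows scale only, under 1:1 allocation. The rule should be changed because the check is cheap and uses results already on file. Unknown frequency keeps it from being more serious than that.

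**What to change.** Add a step before dispensing to the one-week visit text and a matching column to Table 1:

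- The nurse checks the index case's resistance results on file.
- If rifampicin resistance (including on Xpert MTB/Rif), isoniazid resistance or multidrug resistance is documented, isoniazid is not dispensed automatically. A clinician at the study or receiving clinic decides on preventive treatment.
- In these households the referral letter states the exposure to drug-resistant TB. The existing referral-card check, the three home-tracing attempts and the three-month symptom screen apply.
- Contacts of susceptible or untested index cases stay on the current rows.

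Rifampicin belongs in the trigger because Xpert MTB/Rif is on the extraction list and isoniazid susceptibility is not, so rifampicin resistance may be the only resistance on file. It prompts a review and does not presume isoniazid resistance.

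Add the index case's rifampicin and isoniazid susceptibility, where available, to the extraction form in both arms.

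The cost is one procedural step, one table column, one line in the letter, two extraction fields and some clinician time; the household team itself is nurse- and counsellor-led. The real downside is that some contacts, including some infected elsewhere with a susceptible strain, will start preventive therapy later or not at all. The three-month visit section itself reports that many household members diagnosed with TB or HIV at the baseline visit do not reach care, which is why supported linkage must be part of the change.
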